### Data and safety monitoring committee

To ensure patient safety and study integrity, an independent data and safety monitoring committee is established, which will evaluate the progress of the trial and will examine safety parameters at regular intervals of 100 included patients. All involved physicians need to report any potential adverse events encountered in this study and these potential adverse events will be discussed with the monitor committee. The monitoring committee can request a full report in order to discuss a specific adverse event and this report will be sent to the central ethics committee and all involved physicians.

All deceased patients will be evaluated by the safety committee for cause of death and possible trial related serious adverse events. All deaths will be reported to the central ethics committee and the local ethics board. The DSMB consists of an epidemiologist/statistician, an independent surgeon and an independent endocrinologist.

### Power calculation

The data of the randomized subjects are analysed according to the intention to treat principle. Follow up will be completed until 5 years after the operation.

For the sample size determination the used hypothesis for the study are:H0: mean %EBMIL (LSG) = mean %EBMIL (LRYGB)H1: mean %EBMIL (LSG) ≠ mean %EBMIL (LRYGB)

To be able to reject the null hypothesis that mean %EBMIL after LSG treatment equals mean %EBMIL after LRYGB, at least 2×294 analysable patients have to be included (mean (SD) %EBMIL is 68.59 (25.88) after LSG and 62.60 (25.88) after LRYGB; type I error: 0.05 (two sided), type II error = 0.20 (power = 80 %), randomization ratio 1:1). Considering a dropout rate of 5 %, the sample size is estimated to be 2×294/.95 = 2×310 = 620.

The %EBMIL data of LSG and LRYGB are obtained from the meta analysis of Garb *et al.* [35]. The standard deviation of LRGYB is assumed to be equal to the standard deviation of LSG.

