## Abstract

**Background:**

Obesity is an increasing disease worldwide. Bariatric surgery is the only effective therapy to induce sufficient long-term weight loss for morbidly obese patients. Laparoscopic Roux-en-Y Gastric Bypass (LRYGB) is the gold standard surgical technique. Laparoscopic Sleeve Gastrectomy (LSG) is a new promising bariatric procedure which has the advantage of maintaining an intact gastrointestinal tract. The aim of this study is to evaluate the efficiency of both techniques. Our hypothesis is that LSG has a similar percentage excess BMI loss (%EBMIL) after 5 years compared to LRYGB.

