### Hypothesis

Our hypothesis is that LSG has a comparable %EBMIL after 5 years when compared to LRYGB [22–26]. Even if LSG is marginally less effective compared to LRYGB in terms of long term %EBMIL, QOL might be better from a dietary and long term complications point of view [27-29].

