### Study questions

Primary Question: Does LSG result in a similar long term %EBMIL after a follow up period of 5 years when compared to the LRYGB?

Secondary Question: Is the QOL better after a LSG compared with the LRYGB?

Other secondary endpoints: improvement in obesity induced co-morbidity, complication rate, readmission and reoperation rate, revision surgery rate, operating time and duration of hospital stay and the predictive value of sweet eating habit inventoried by the Dutch Sweet Eating Questionnaire (DSEQ) [21].

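### The stated hypothesis is similar 5-year weight loss, but the planned test takes equality as its null and has no margin, so it cannot establish similarity and the 80% power answers another question

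*Protocol article*

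**What the plan says.** Three places in the protocol article frame the primary aim as similarity:

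- Abstract, Background: "Our hypothesis is that LSG has a similar percentage excess BMI loss (%EBMIL) after 5 years compared to LRYGB".
- Hypothesis: "Our hypothesis is that LSG has a comparable %EBMIL after 5 years when compared to LRYGB". The same section then allows for a small deficit: "Even if LSG is marginally less effective compared to LRYGB in terms of long term %EBMIL, QOL might be better".
- Study questions, put as the primary one: "Does LSG result in a similar long term %EBMIL after a follow up period of 5 years when compared to the LRYGB".

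The Power calculation section sets up a different problem. The null is "H0: mean %EBMIL (LSG) = mean %EBMIL (LRYGB" and the alternative is "H1: mean %EBMIL (LSG) ≠ mean %EBMIL (LRYGB", each for the two arm means. The purpose of the sample size is given as "To be able to reject the null hypothesis that mean %EBMIL after LSG treatment equals mean %EBMIL after LRYGB, at least 2×294 analysable patients". The planning values are "mean (SD) %EBMIL is 68.59 (25.88) after LSG and 62.60 (25.88) after LRYGB", with a two-sided type I error of 0.05, 80% power, 1:1 allocation and 5% dropout, giving 620 in total.

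The article gives no equivalence or non-inferiority margin, and no confidence-interval criterion for calling the two procedures similar.

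**The concern.** A test with equality as its null can produce evidence of a difference. It cannot produce evidence of similarity. If it rejects, the trial's own hypothesis is contradicted. If it does not reject, the result is compatible with equality but also with differences that may matter clinically. Neither outcome answers the primary question as asked.

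The stated power has the same problem. It is the chance of declaring the arms different when they truly differ by 5.99 points. Under the hypothesis the investigators hold, with arms equal or nearly so, that figure does not describe the chance of reaching the hoped-for conclusion.

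This affects what the trial can claim. The Discussion part of the abstract makes the choice between techniques turn on comorbidity and quality of life once weight loss is found comparable. The Hypothesis section accepts that LSG may be slightly less effective, and the Background section records a worry that the sleeve's effect fades with time. A modest LSG deficit is therefore a scenario the article itself raises, yet nothing says how large a deficit would still count as comparable.

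**Working it through.** **Inputs**, all from the Power calculation section: means 68.59 and 62.60, so a planning difference of 68.59 − 62.60 = 5.99 points; common SD 25.88; two-sided alpha 0.05; power 80%; 294 analysable per arm; 5% dropout.

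**1. Reproducing the plan's figure.**

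n per arm = 2 × (1.96 + 0.8416)² × 25.88² / 5.99² = 293.03, rounded up to 294. A noncentral-t check at 294 gives 80.0%. Dropout: 294 / 0.95 = 309.5, rounded up to 310 per arm, 620 in total. The arithmetic is right for a two-sided test of difference.

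**2. Precision at the planned size.**

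SE = 25.88 × √(2/294) = 2.13 points. The 95% CI half-width is 1.96 × 2.1345 = 4.18 points.

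**3. What the stated test does at various true differences.**

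P(reject) = Φ(δ/SE − 1.96) + Φ(−δ/SE − 1.96), where δ is the size of the true difference in either direction.

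| True difference (points) | P(reject equality) | P(non-significant) |
|---|---|---|
| 0 | 5% | 95% |
| 3 | 29% | 71% |
| 4 | 47% | 53% |
| 5 | 65% | 35% |
| 5.99 | 80% | 20% |

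A non-significant result is thus the more likely outcome at a true difference of 3 or 4 points, and it is far from rare at 5.

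**4. What the same 294 per arm would give for a similarity claim.**

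The article has no margin, so the margins M below are assumptions. So is a true difference of 0; SD is 25.88.

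Non-inferiority, one-sided 2.5%: power = Φ(M/SE − 1.96).

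- M = 4: Φ(1.874 − 1.96) = 47%
- M = 5: Φ(2.342 − 1.96) = 65%
- M = 5.99: Φ(2.806 − 1.96) = 80%

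Equivalence at M = 5.99: power = 2Φ(M/SE − z) − 1.

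- Two one-sided tests at 5% each (z = 1.645): 2Φ(1.161) − 1 = 75%
- 95% CI wholly inside ±M (z = 1.96): 2Φ(0.846) − 1 = 60%

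At a margin of 4 points, equivalence by 95% CI is out of reach at the planned SD, because the half-width of 4.18 already exceeds the margin.

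**5. Total sample size needed for 80% non-inferiority power** (same assumptions, 5% dropout): 620 at M = 5.99, 888 at M = 5, 1386 at M = 4, 2462 at M = 3.

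**The case against.** The best defence is that the formal aim is neutral. The Study objective and Study design sections speak only of comparing %EBMIL between the procedures, and a two-sided difference test fits that. The two hypotheses are also introduced for sample size purposes, and a separate analysis plan may set a margin or an interval-based reading. This has weight: it makes rewording the aim as legitimate a repair as adding a margin. It does not remove the mismatch. The hypothesis and the primary question are printed as similarity, while H0, H1 and the basis of the power are printed as difference. An analysis plan that added a margin would then disagree with this article.

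Four stronger readings are tempting, and the document does not support them:

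- *The trial is powered in the wrong direction, because planning assumes LSG is better.* The test is two-sided with a common SD and equal allocation, so it has the same 80% power against a 5.99-point LSG deficit.
- *A non-significant p-value will be reported as similarity.* No section says so. It is a risk left open by the lack of any other decision rule, not a stated plan.
- *Missing data, crossover and revision surgery all push towards apparent similarity.* This is not shown. Informative missingness or differential revision could bias the difference either way.
- *The sample size is wrong, or says nothing about similarity.* The planned precision of about ±4.2 points is informative. Whether 620 is enough depends on a margin that the article does not give; 5.99 is used there only as a difference to detect.

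**Conclusion.** The point holds in this form: the stated test cannot establish the stated hypothesis, and the 80% is power for a different question. The sample size arithmetic is correct, and 620 is not shown to be too few.

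If the arms are truly equal, the planned test rejects 5% of the time. If they truly differ by 3, 4 or 5 points, it is non-significant with probability 71%, 53% or 35%. These figures assume the planned 294 analysable per arm and the SD of 25.88. The power figures for non-inferiority and equivalence further assume a true difference of 0 and margins that are illustrative.

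This should be corrected, because it governs what the primary analysis may conclude and can be put right without enrolling more patients.

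**What to change.** Choose one of two routes.

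**(a) Keep the similarity aim.** Before any 5-year comparative results are known, fix a clinically justified margin. Restate the hypotheses as non-inferiority (H0: LSG mean minus LRYGB mean ≤ −margin) or equivalence (H0: absolute difference ≥ margin). Judge them by the 95% CI of the difference in the intention-to-treat and per-protocol analyses already planned under Escape surgery. Keep the two-sided difference test as a follow-on. Restate the power of the existing 620 for the chosen margin, using the figures in the working as a guide.

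**(b) Keep the test.** Reword the hypothesis and primary question as a two-sided test of difference in 5-year %EBMIL. State that a non-significant result will be reported with its CI and not as evidence of similarity.

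**Cost.** Route (b) is wording only, at the price of a narrower claim. Route (a) needs a justified margin and a restated power. For non-inferiority, the existing 620 keeps 80% only if that margin is about 6 points or more. With a smaller margin, the sponsor must accept and state a lower power, or enrol more to restore 80%. Equivalence at 5.99 has to be stated at about 75% or 60%, depending on the criterion.

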## Discussion

Laparoscopic sleeve gastrectomy (LSG) is a relative new procedure which was first described by Marceau and Hess in the 1990s as a part of the BPD duodenal switch and LSG is later popularized by Regan and Gagner as a first stage procedure prior to a duodenal switch (DS) in super obese patients to reduce treatment related mortality [32]. The weight loss results following LSG were excellent, resulting in a second stage procedure in only a quarter of the patients. Therefore, LSG is currently used as a single stage procedure in morbidly obese patients resulting in a percentage excess BMI loss (%EBMIL) ranging between 50 % and 83 % and having a favourable impact on comorbidities [18–22]. In comparison with LRYGB, LSG is technically more simple and faster to perform. However, currently long term results of LSG are limited compared to LRYGB. Another benefit of LSG is the relatively normal dietary options for the patients, potentially improving QOL in comparison with LRYGB. LRYGB associated dumping syndrome, caused by large particles and carbohydrates directly entering the small intestine, has been reported [23, 24]. Moreover, patients treated by LSG have less nutritional deficits compared to LRYGB [25]. Another benefit of LSG is that, as the normal gastrointestinal tract is preserved, diagnostic and therapeutic interventions such as gastroscopy and ERCP are still possible. Especially the inability to perform an ERCP can be a problem after LRYGB as many morbidly obese patients suffer from bile stone related problems following bariatric surgery as a result of weight loss and concurrent cholecystectomy has been abandoned since this can increase perioperative risks and complications. Furthermore, LSG can easily be converted to LRYGB, BPD-DS or an omega loop bypass depending on the patient characteristics and the preferences of the surgeon in case of insufficient weight reduction. Moreover LSG results in a better QOL than LRYGB [9].

Currently, only few randomized controlled trials have compared LSG and LRYGB [11, 19]. However, these studies described small study groups and did not report long-term results. Although their conclusions lack hard evidence to determine in which patients these two different techniques should be performed, these studies seem to show a small short term beneficial result for LSG.

This study will contribute to the evidence of the benefits of LSG versus the standard LRYGB.
